
### Interim analysis and monitoring

2.5

Because this is a short-term pilot study with a 12-month follow-up, we will not conduct interim analysis for the clinical efficacy of oral ALA-SFC. However, the safety of ALA-SFC will be independently evaluated by the Data and Safety Monitoring Committee at the time as follows:i)Critical modification of the study protocol is requiredii)Any serious adverse event associated with this agent occursiii)A critical problem is observed while monitoringiv)The principal investigator needs the judgement of this committee

Moreover, the monitoring committee independently evaluates whether the study is implemented in compliance with the study protocol, and the data are appropriately corrected according to a pre-arranged monitoring plan at the time when the first patients have been enrolled and once per year.

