Studies over the past several decades have investigated the pathophysiological and molecular mechanisms underlying radiotherapy-induced effects on both tumor tissue and normal tissue [6,7]. Although several pharmacological interventions that potentially prevent radiation-induced damage in normal tissues have been explored in preclinical studies, only a couple of them have progressed to clinical use [6]. Our previous study was the first to demonstrate the dual benefit of supplementary oral 5-aminolevulinic acid (ALA) and pelvic radiotherapy in a syngenic PCa model, i.e., MyC-CaP cells in FVB mice [7]. The “dual benefit” includes radiosensitization of PCa tumor tissues and radioprotection of normal pelvic organs from radiotherapy. ALA is distributed ubiquitously in mammalian cells and is a precursor of porphyrins and heme protein, which play essential roles in aerobic energy metabolism and the electron transport system [8]. Preclinical studies have demonstrated that ALA can confer a broad range of cytoprotective effects against cisplatin-induced nephrotoxicity, rhabdomyolysis-induced acute kidney injury, hypoxia-induced cardiomyocyte injury, and neurotoxicity in preclinical studies [[9], [10], [11], [12]]. Based on the results, an interventional single-arm clinical trial is ongoing to evaluate whether oral ALA phosphate with sodium ferrous citrate (ALA-SFC) prevents cisplatin-induced renal injury in patients with unresectable gastric cancer (trial ID: UMIN000024642). Moreover, Japanese double-blinded, randomized, placebo-controlled trials are ongoing to investigate the clinical benefit of oral ALA-SFC for patients with mitochondrial disease (JMA-IIA00358), Alzheimer disease (jRCTs041180135), and autism spectrum disorder (jRCTs051190017).

This prospective, open-label, single-center, single-arm pilot trial evaluates the short-term toxicity, such as urinary frequency, and other types of complications of LDR-BT. The intervention in this trial is oral administration of ALA-SFC, which is widely accepted as a health supplement and food with functional claims. Based on the results obtained in this trial, we will design a double-blinded, randomized, placebo-controlled trial to consolidate the clinical value of this intervention. To the best of our knowledge, this is the first study investigating the potential clinical benefit of oral ALA-SFC after radiotherapy and is expected to lead to better post-radiotherapy management.

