## Discussion

3

It has been more than 15 years since LDR-BT was introduced in Japan [2]. A comprehensive review reported excellent oncological outcomes showing equivalent or superior efficacy to radical prostatectomy for low- or intermediate-risk PCa and superiority for high-risk PCa based on the experience of more than 52,000 patients undergoing LDR-BT with or without EBRT [2]. However, there are still significant concerns about side effects, complications, and consequently reduced QOL after radiotherapy. One of our long-term interests is worsening lower urinary tract symptoms. Most urinary adverse events are categorized into grade 1 to 2, while higher-severity adverse events are rare. More than 70% of patients experience increased urinary frequency (pollakiuria) during the first 6 months after seed implantation [19]. To overcome this clinical issue, our group and other groups have conducted randomized controlled trials to explore medications preventing post-treatment urinary adverse events. However, the true benefits of α1-adrenoceptor antagonists, anti-cholinergic drugs, β3-adrenoceptor agonists, phytotherapeutic drugs, and non-steroidal anti-inflammatory drugs have not been proven yet [14,[20], [21], [22]].

We plan to evaluate whether oral ALA-SFC prevents GU toxicities after seed implantation. ALA-SFC is widely accepted as a health supplement and food with functional claims in Japan. This product reportedly inhibits elevations in blood glucose level, improves sleep quality, and supports muscle strength and exercise efficiency [23,24]. Moreover, preclinical studies have demonstrated that ALA confers cytoprotective effects in the bladder, rectum, kidney, heart, and neural system from various types of stress [7,[9], [10], [11], [12]]. Another potential benefit of adding ALA is an increase in the radiosensitization of malignant cells. Previous research has shown that ALA supplementation sensitizes malignant cells including glioma, melanoma, and colon adenocarcinoma cells to radiotherapy via enhanced generation of protoporphyrin IX and reactive oxygen species [7]. Our previous preclinical study confirmed that adding *in vitro* single and *in vivo* repeated administration of ALA sensitized PCa cells to radiotherapy. Based on this evidence, this trial includes oncological outcomes such as biochemical recurrence-free survival as secondary endpoints.

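### The only adverse-event trigger for safety committee review depends on association with ALA-SFC, so independent review of serious events judged implant-related is not assured

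*Protocol article*

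**What the plan says.** Section 2.5 (Interim analysis and monitoring) rules out an interim look at efficacy: "we will not conduct interim analysis for the clinical efficacy of oral ALA-SFC". It then states that "the safety of ALA-SFC will be independently evaluated by the Data and Safety Monitoring Committee" on four listed occasions:

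- Item i: a critical change to the protocol.
- Item ii: a "serious adverse event associated with this agent".
- Item iii: a critical problem seen during monitoring, not further defined.
- Item iv: "The principal investigator needs the judgement of this committee".

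A separate activity is scheduled for when the first patients have been enrolled and then yearly. In it, "the monitoring committee independently evaluates whether the study is implemented in compliance with the study protocol", and data handling is checked. Review of event rates is not mentioned there.

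Three other places bear on item ii:

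- The Introduction describes the design: "This prospective, open-label, single-center, single-arm pilot trial evaluates the short-term toxicity". It also gives the agent's proposed action, from a mouse model: "radiosensitization of PCa tumor tissues and radioprotection of normal pelvic organs from radiotherapy".
- The Introduction names GI and GU complications as known consequences of the implant.
- Section 2.3 has the investigators, who are unblinded according to section 2.1, assess adverse events using CTCAE v5.0.

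**The concern.** A trigger based on relatedness works when an event caused by the agent can be told apart from an event caused by something else. That is hard here. A serious bladder, urethral or rectal event after seed implantation is a recognised complication of the implant. If the agent changed the likelihood or severity of such events, the individual case would look the same. There is no concurrent untreated arm, and the assessor knows that the patient takes ALA-SFC. Causation can be addressed only by comparing frequencies, and item ii does not call for that.

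At stake is whether the independent committee is certain to see the serious events that matter most when a proposed modifier of the radiation response is first combined with radiotherapy in patients. As item ii is worded, that depends on a case-by-case judgement that the design cannot support.

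**Working it through.** **No plan figure to reproduce.** The document gives no serious-event rate and no monitoring threshold. The check is a reading of the trigger list, followed by an illustration on assumed rates.

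**Step 1: how a serious event judged implant-related can reach the committee.**

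| Route in section 2.5 | Defined by an adverse event? | Covers an event judged implant-related? |
|---|---|---|
| i, critical protocol change | No | Only if the protocol is being changed |
| ii, serious event associated with the agent | Yes | No, if it is judged not associated |
| iii, critical problem in monitoring | No, undefined | Possibly, by judgement |
| iv, principal investigator's request | No | Possibly, by choice |
| Scheduled monitoring | No, compliance and data | Not as a review of safety |

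No mandatory route remains for such an event. Routes iii and iv stay open but are discretionary.

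**Step 2: is association a dependable filter here?** Three statements in the document count against it: GU and GI injury is expected from the implant alone (Introduction), the agent is proposed to act on the radiation response (Introduction), and the design is open-label with a single arm (Introduction, section 2.1). In normal tissue the proposed effect is protective, but the evidence for it is preclinical, and the article describes this as the first clinical study of oral ALA-SFC after radiotherapy. The effect on human pelvic tissue is untested in either direction.

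**Step 3: illustration.** Inputs:

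- n = 50 trial cases (section 2.4).
- p = probability that a patient has a serious event, assumed to be 0.02 to 0.06.
- q = probability that such an event is judged associated with the agent, assumed to be 0, 0.10 or 0.25. The value q = 1 stands for no attribution condition.

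The Discussion says only that "Most urinary adverse events are categorized into grade 1 to 2, while higher-severity adverse events are rare". That concerns severity grade for urinary events, which is not the same as seriousness, so it does not supply p.

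Expected events: n × p = 50 × 0.02 = 1, up to 50 × 0.06 = 3.

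Chance of at least one event: 1 − (1 − p)^50 = 1 − 0.98^50 = 0.64, up to 1 − 0.94^50 = 0.95.

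Chance that item ii never fires: (1 − p × q)^50.

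| q | p = 0.02 | p = 0.06 |
|---|---|---|
| 0 (all judged implant-related) | 1.00 | 1.00 |
| 0.10 | 0.998^50 = 0.90 | 0.994^50 = 0.74 |
| 0.25 | 0.995^50 = 0.78 | 0.985^50 = 0.47 |
| 1 (no attribution condition) | 0.98^50 = 0.36 | 0.94^50 = 0.05 |

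The values depend on the assumptions. The direction does not: for any q below 1, the condition lowers the chance that the committee is called under item ii.

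**Step 4: what a historical rate could add.** With 50 trial cases and 150 historical controls (section 2.4), 3/50 against 3/150 gives a two-sided Fisher exact p of 0.17. True rates of 6% against 2% would reach p < 0.05 about 27% of the time, and 4% against 2% about 12%, even with all 50 patients complete. A historical frequency is useful context for the committee but cannot serve as a formal test.

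**The case against.** The strongest objection is that nothing in the document predicts more normal-tissue injury. The Introduction proposes protection of pelvic organs, and the Discussion reports cytoprotection in bladder and rectum. This stands. Harm is a possibility to watch for, and a reader who infers that it is the trial's main safety hypothesis goes beyond the text.

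A reader might also infer that radiation-type injury is screened out of committee review. The document does not support that. Items iii and iv carry no attribution condition, so such events can still be referred. Section 2.3 records GU and GI toxicity without an attribution filter, and section 2.4 plans a comparison of trial data with historical controls. What remains is that referral to the independent committee during the trial is discretionary.

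The article does not define association or say who judges it. An implant-related event might be read as also associated with the agent. That is fair, but it means that the wording does not settle whether the committee sees the event.

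The article condenses a full protocol and refers to a monitoring plan that is not shown. Wider serious-event reporting rules may exist there, and their absence from the article is no fault. The point rests only on the wording that the article gives for item ii.

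Finally, if single cases cannot separate agent from implant, a few more single-case reviews will not establish causation, and the power figures confirm this. That limits the benefit. It does not remove the value of letting an independent body see every serious event.

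**Conclusion.** The point holds in limited form. The only committee trigger defined by adverse events requires association with ALA-SFC, a judgement that this design does not allow to be made reliably for radiation-type injury. Independent review of a serious event judged implant-related is therefore not assured, though it is not excluded.

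The size is modest: about 1 to 3 serious events among 50 patients, if 2% to 6% have one. That range is assumed. The conclusion about the wording does not depend on it, but it does depend on reading item ii as excluding events judged due to the implant alone.

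No figure in the plan is wrong and no passages contradict each other. This is an inexpensive improvement to safety oversight.

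**What to change.** In section 2.5, reword item ii to: *any serious adverse event during ALA-SFC treatment and follow-up, whatever the attributed cause*. The investigator's view of causality can still be recorded and passed to the committee, but it should not decide whether the committee is told.

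Where it can be obtained, also give the committee the frequency of serious GU and GI events in the historical controls, labelled as descriptive context and not as a test.

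The cost is one phrase in the protocol and, on the assumed rates, at most about 1 to 3 additional reviews by a committee that already exists. Retrieving the historical frequency takes some chart work on a series that is already being assembled. The change affects only which events are referred for review. It leaves dose, treatment and discontinuation criteria as they are.

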### Statistical analysis

2.6

Descriptive statistics will be computed for all study variables. Comparison of the two groups, the trial cases and historical control cases, will be conducted using the Mann–Whitney *U* test or Wilcoxon signed rank test for continuous variables, and Fisher's exact test or Tarone test for categorical variables as appropriate. Survival analysis will be conducted using the Kaplan–Meier method and log-rank test. P < 0.05 will be considered statistically significant.

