### Procedure of LDR-BT

2.2

As of November 30, 2019, we have an LDR-BT treatment experiment of more than 1400 patients. The detailed procedure of the seed implantation has been previously described [13,14]. All the patients are hospitalized for 3 nights and 4 days. The prescribed radiation dose is 160 Gy for the monotherapy. For patients without any contraindications, SpaceOAR™ hydrogel is injected between the rectum and prostate to minimize high-dose radiation to the rectum and consequent bowel side effects. Experienced radiation oncologists ([name] and [name]) calculate the post-implant dosimetric parameters based on a pelvic computed tomography scan performed about 1 month after LDR-BT.

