### Determining the target sample size

2.4

To date, we have been working on several clinical studies regarding oncological outcomes, adverse events, complications, and changes in urinary frequency and PROs among patients undergoing LDR-BT [3,4,14,17,18]. In this study, the data of the trial cases will be compared with historical control data. Data of patients who underwent seed implantation monotherapy between February 2016 and February 2019 will be extracted for the historical control data. The primary endpoint of this trial is urinary frequency 3 months after the implantation. One of our previous studies showed that a significant increase in urinary frequency and significant decrease in mean voided volume persisted for 12 months after seed implantation [14]. The average times per day of urination increased from 9.2 at baseline to 12.2 at 3 months after seed implantation because of bladder irritability. This observation indicated that the increase in urinary frequency was 3 times per day at 3 months, which was the peak point. To determine the required sample size of this trial, we expect that oral ALA-SFC can suppress the increase in urinary frequency to only 1 time per day and estimate the standard deviation of urinary frequency to be 3.5 times both in trial cases and historical control cases. The ratio of case numbers is set to 1:3 for trial cases and historical control cases, respectively. Given the 10% proportion of ineligible patients, the required sample size was determined to be at least 37 for trial cases and 109 for historical control cases to provide 80% power (β = 0.20) and an α level of 0.05 (two-sided). Based on the estimation, a total of 50 trial cases and 150 historical control cases will be enrolled in this study. The historical data will be obtained from consecutive patients undergoing LDR-BT with or without short-term ADT between January 2016 and January 2019. Patients who received prophylaxis with 50 mg of mirabegron (a β3-adrenoceptor agonist) just after seed implantation for decreasing undesired urgency and urinary frequency will be excluded from the historical control cases. Patients who received supplementary extra-beam radiotherapy will be excluded from the historical control cases. Pre- and post-treatment clinicopathologic factors are compared between two groups: age, body mass index, comorbidities, pretreatment urinary frequency, pretreatment PSA level, pretreatment prostate volume, biopsy Gleason score, clinical tumor stage, D'Amico risk stratification, and the post-implant dosimetric parameters.

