## Trial status

The study began in December 2019. Patient recruitment has not yet been completed and the intervention program is ongoing. A follow-up and data collection will be completed in March 2022. The final results are expected in September 2022.

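### The primary comparison with non-randomised historical controls is specified only as an unadjusted two-group test, so measured case-mix differences, including baseline urinary frequency, can bias it in either direction

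*Protocol article*

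**What the plan says.** The Introduction describes the design: "This prospective, open-label, single-center, single-arm pilot trial evaluates the short-term toxicity". Section 2.4 supplies the comparator: "In this study, the data of the trial cases will be compared with historical control data".

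Section 2.4 gives the control period twice. One sentence reads "Data of patients who underwent seed implantation monotherapy between February 2016 and February 2019 will be extracted for the historical control data"; a later one refers to "consecutive patients undergoing LDR-BT with or without short-term ADT between January 2016 and January 2019". These need reconciling, but neither window overlaps recruitment, because under Trial status "The study began in December 2019".

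Section 2.6 fixes the between-group methods: "Comparison of the two groups, the trial cases and historical control cases, will be conducted using the Mann–Whitney" U test. It goes on to name methods by type of variable, as appropriate: Mann–Whitney U or Wilcoxon signed rank for continuous variables, Fisher's exact or Tarone for categorical variables, and Kaplan–Meier with log-rank for survival. The significance criterion is P < 0.05.

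On prognostic factors, section 2.4 says: "Pre- and post-treatment clinicopathologic factors are compared between two groups: age, body mass index, comorbidities, pretreatment urinary frequency". The list continues with PSA, prostate volume, Gleason score, stage, D'Amico risk and post-implant dosimetry. Nothing is said about using these factors in the efficacy comparison. Neoadjuvant ADT, allowed in both groups, is not on the list.

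**The concern.** Without randomisation, a two-group P value has its nominal 5% error rate only if the groups would have had the same outcome distribution without the drug. Comparing covariates between groups describes an imbalance but does not remove its effect on the endpoint. A non-significant baseline comparison is also weak reassurance at this sample size.

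The sample-size argument makes baseline frequency especially important. The target of 2/day is a difference between two increases from baseline (+3 and +1), while the endpoint is worded as the frequency at 3 months. The two coincide only if both groups start from the same level, and the stated tests do not secure that.

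The Introduction says the results will be used to design a placebo-controlled trial. A biased estimate, whether inflated or masked, would carry over into that design.

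**Working it through.** **Inputs (section 2.4).** Control increase 12.2 − 9.2 = 3/day; expected increase on ALA-SFC 1/day; target difference 2/day; SD 3.5/day in both groups; ratio 1:3; two-sided α 0.05; power 80%; 10% ineligible; enrolment 50 and 150.

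**Reproducing the plan's sample size.** Trial n = (1.96 + 0.842)² × 3.5² × (1 + 1/3) / 2² ≈ 32.1, so 33 trial cases and 99 controls. Adding 10% gives 33 × 1.1 = 36.3 → 37 and 99 × 1.1 = 108.9 → 109, the stated 37 and 109. The sample size is not in question.

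**Precision at 50 versus 150.** SE = 3.5 × √(1/50 + 1/150) = 0.5715/day. An observed difference of 1.96 × 0.5715 = 1.12/day is significant. Power for 2/day is about 94%.

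**Type I error under a case-mix shift.** Assume no drug effect and a shift d in mean 3-month frequency. The documents give no size for d, so a range is shown. Rejection rate = Φ(−1.96 + d/SE) + Φ(−1.96 − d/SE).

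| Assumed shift at 3 months | Normal approximation | Simulated Mann–Whitney (4,000 runs, normal data) |
|---|---|---|
| 0 | 5% | 4.7% |
| 0.5/day | 14% | 13.5% |
| 1.0/day | 42% | 38.7% |
| 1.5/day | 75% | 71.2% |

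**From a baseline gap to a 3-month shift.** A baseline gap is not carried over in full. With equal SDs at both times and correlation r, a gap of 1/day predicts a 3-month shift of r × 1. For an assumed r of 0.3–0.7:
- r = 0.3: d/SE = 0.3/0.5715 = 0.52, rejection about 8%.
- r = 0.7: d/SE = 0.7/0.5715 = 1.22, rejection about 23%.

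**Would the planned baseline comparison reveal such a gap?** If the baseline SD is also 3.5 (assumption), a true baseline gap of 1/day reaches P < 0.05 only about 42% of the time, from the same formula at d = 1.0.

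**Price of adjusting.** The residual SD after adjusting for baseline is 3.5 × √(1 − r²).

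| Assumed r | Residual SD | Power for 2/day at 50 vs 150 |
|---|---|---|
| Unadjusted | 3.50 | 94% |
| 0.3 | 3.34 | 96% |
| 0.5 | 3.03 | 98% |
| 0.7 | 2.50 | above 99% |

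These powers are before any loss from covariate imbalance between the groups.

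**The case against.** **Section 2.6 is short and lists tests by variable type; it does not rule out adjustment.** This is true, and a fuller protocol (version 1.0) exists that is not shown. A reader might infer that the plan forbids adjustment; it does not. But it does name the methods for this comparison, and none of them adjusts the primary endpoint. The signed rank test needs pairs, and no pairing of cases with controls is described. The Tarone test is listed for categorical variables only.

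**The target may be the change from baseline.** The sample size uses increases, and the Discussion speaks of preventing an increase. Analysing change would handle baseline only in part: under the same assumptions a 1/day baseline gap leaves r − 1, that is 0.3–0.7/day in the opposite direction. The endpoint is in any case worded as the 3-month frequency.

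**Confounding is already limited.** Controls are consecutive patients from the same centre, EBRT is excluded in both groups, short-term ADT is allowed in both, and prophylactic mirabegron users are removed from the controls. The study is called a pilot, and the abstract says a randomised trial is needed to change care. All of this stands. It lowers the likely bias and the stakes, but leaves P < 0.05 on an unadjusted test as the stated criterion.

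**Adjustment cannot cure the era problem.** This also stands. Era coincides completely with group, so a reader who infers that regression would make the comparison equivalent to a randomised one would be wrong.

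**Other omitted factors.** Spacer use ("For patients without any contraindications, SpaceOAR™ hydrogel is injected between the rectum and prostate") concerns the rectum and is peripheral to urinary frequency. Nothing shows that spacer or α1-antagonist use can be retrieved for the controls.

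**Conclusion.** The point holds for measured case-mix. As stated, the non-randomised primary comparison is unadjusted, and baseline frequency and other prognostic factors are compared without being used.

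The size is conditional. With SD 3.5, 50 versus 150 and no drug effect, the two-sided type I error is about 14% at an assumed 3-month shift of 0.5/day and about 39–42% at 1.0/day. For an assumed 1/day baseline gap with correlation 0.3–0.7 it is about 8–23%.

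A reader might infer that a significant result would be an artefact, or that a 1/day baseline gap alone brings the error to about 42%. The documents support neither: the size and direction of any imbalance are unknown, it could equally mask a benefit, and the 42% belongs to a 1/day shift in the outcome itself.

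**What to change.** In section 2.6, before the groups are compared:

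- Make the primary analysis a linear regression of 3-month 24-h urinary frequency on group, adjusted for baseline frequency and a short list of pre-implant factors available in both groups: age, prostate volume, neoadjuvant ADT and D'Amico risk. Propensity-score weighting on the same factors is an alternative.
- Report the adjusted difference in voids per day with a 95% CI, using robust or bootstrap standard errors. Keep Mann–Whitney as an unadjusted sensitivity analysis.
- Add neoadjuvant ADT to the section 2.4 factor list. Add α1-antagonist use at implantation to the model only if it can be retrieved for the controls.
- Leave post-implant dosimetry out of the primary model, because it is measured about 1 month after implantation, when ALA-SFC has already started.
- State that adjustment cannot remove unmeasured and era differences, so the result is hypothesis-generating for the planned randomised trial.
- Reconcile the two control windows.

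The cost is a few sentences, a little more analysis work and reliance on chart data for the controls. No extra patients are needed.

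### Section 2.6 assigns a paired test (Wilcoxon signed rank) and an undefined Tarone test to the comparison of two unmatched groups; the impact is limited and the wording needs correcting

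*Protocol article*

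**What the plan says.** Section 2.6 (Statistical analysis) sets the scope of its test list at the start of the sentence: "Comparison of the two groups, the trial cases and historical control cases, will be conducted using the Mann–Whitney" U test or, as the alternative, the "Wilcoxon signed rank test for continuous variables". For categorical variables it gives "Fisher's exact test or Tarone test for categorical variables as appropriate". The next sentence deals separately with survival outcomes, by Kaplan–Meier and log-rank. No test is tied by name to the primary endpoint.

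Section 2.4 (Determining the target sample size) describes the groups. On the controls it says: "The historical data will be obtained from consecutive patients undergoing LDR-BT with or without short-term ADT between January 2016 and January 2019". On the ratio: "The ratio of case numbers is set to 1:3 for trial cases and historical control cases, respectively". On the planned numbers: "a total of 50 trial cases and 150 historical control cases will be enrolled in this study". On the endpoint: "The primary endpoint of this trial is urinary frequency 3 months after the implantation". Matching or pairing of treated patients to controls is not described. Section 2.4 lists baseline and dosimetric factors to be compared between the groups, among them pretreatment urinary frequency.

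**The concern.** The signed rank test works on paired differences or on a single sample. It is listed here for a comparison of two separate sets of patients, of unequal size and treated in different years. The Tarone test is a second difficulty. The name is attached to more than one procedure, and the document does not say which is meant. Its usual meaning with categorical data is a test that odds ratios are homogeneous across strata, and no strata are named. The other common meaning, Tarone–Ware, is a weighted log-rank test for survival data.

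What is at stake is clarity about which P value answers the trial's question. The one natural use of signed rank in this design is change from baseline within the treated group. Two other places make that use easy to picture: the Introduction calls the trial single-arm, and the Discussion describes the primary endpoint as preventing a rise in frequency. A within-arm P value could then be taken as evidence on ALA-SFC although the controls play no part in it.

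**Working it through.** **1. Inputs (section 2.4).** Untreated patients go from 9.2 to 12.2 voids per day at 3 months, a rise of 3. The hoped-for rise on ALA-SFC is 1, so the between-group difference is 3 − 1 = 2. The SD is 3.5 in both groups, the ratio 1:3, two-sided α 0.05, power 80%, ineligible proportion 10%.

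**2. The plan's own sample size.** For two independent means with three controls per treated patient:

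n(trial) = (1 + 1/3) × [3.5 × (1.960 + 0.842) / 2]² = 32.05, and n(control) = 3 × 32.05 = 96.15.

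The noncentral t version gives 32.54 and 97.61. Dividing by 0.90 gives 36.15 and 108.46, which round up to the stated 37 and 109. The study was therefore sized as a comparison of two independent samples, and the paired test in section 2.6 does not fit that design.

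**3. Signed rank between the groups.** Each value needs a partner. With 50 values on one side and 150 on the other, and no pairing rule, the statistic is not defined. An attempt to run it stops on incompatible lengths.

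**4. Signed rank within the treated group.** This can be computed, but its null hypothesis is no change from baseline. The SD of change is not in the document (3.5 is the SD of frequency), so I assume 2.5 to 4.5. If the SD is 3.5 at both times, SD of change = 3.5 × √[2(1 − ρ)], and this range corresponds to a baseline-to-follow-up correlation ρ of about 0.74 down to 0.17. Rejection rates with n = 50, normal data and 2,000 simulated trials per cell:

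| Mean rise per day | SD 2.5 | SD 3.5 | SD 4.5 |
|---|---|---|---|
| 3 (no drug effect) | 100% | 100% | 99% |
| 1 (hoped-for effect) | 78% | 48% | 32% |

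A hand check of the middle cell of the second row: 1 / (3.5/√50) = 2.02 standard errors, power about 0.52 by normal approximation. A significant result here means that frequency changed after implantation, which is expected with or without the drug. A non-significant result, which occurs in 22% to 68% of trials when the rise is 1, could be misread as prevention. Neither outcome compares the treated patients with the controls.

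**5. Tarone test, taken as homogeneity of odds ratios.** Illustrative assumption: two strata of 25 treated and 75 controls, 2,000 simulated trials.

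| Event rates, treated vs control | Tarone-adjusted homogeneity test | Mantel–Haenszel test |
|---|---|---|
| 0.7 vs 0.7 | 5.1% | 5.0% |
| 0.4 vs 0.7 | 4.7% | 96% |

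Under this reading the test stays at its null level when the groups differ greatly, because the odds ratio is the same in both strata.

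**6. What remains if both names are removed.** Simulated Mann–Whitney U power (normal data, means 10.2 and 12.2, SD 3.5, 4,000 trials each) is 0.92 at 50/150, 0.90 at 45/135 (10% removed from each group) and 0.785 at 33/98 (step 2 before inflation, rounded up). Type I error is 0.047 to 0.055. The planned numbers need no change.

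**The case against.** The strongest defence is that nothing invalid can result between the groups. Signed rank cannot be executed there, so Mann–Whitney U, named first in the same sentence, is the only usable option for continuous data. Fisher's exact test covers categorical data, and the qualifier at the end of the sentence leaves the analyst free to use only the suitable tests. The authors may have meant the rank sum test, or signed rank for within-patient change. All of this stands as a limit on the impact. It does not make the sentence right: it states a paired test for unpaired groups, so this is not a detail left to a fuller document. The 1:3 ratio does not rescue it either. The controls are consecutive patients, not matched sets, and signed rank would not apply directly to sets of one and three.

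Three stronger readings are tempting, and the document does not support them.

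- A reader might infer that the plan permits a within-arm P value to stand as the treatment comparison. Section 2.6 speaks only of comparing the two groups and names no within-arm efficacy test, so this is a risk of misreading and not a stated analysis.
- A reader might infer that a within-arm test would behave the same whatever the drug does. It would not: a rise of 1 per day is itself the assumed drug effect, and the rejection rate falls from 99–100% to 32–78% as the rise goes from 3 to 1. The fault is the wrong null hypothesis.
- A reader might infer that the Tarone test is certainly wrong. The term is undefined, so the supportable criticism is ambiguity plus poor fit under the usual meanings.

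**Conclusion.** Section 2.6 is wrong as written, with limited consequence. That signed rank is misassigned is firm. It rests on the stated scope of the sentence, the unmatched groups of 50 and 150, and a sample size that reproduces exactly as two independent samples. The Tarone point is conditional on the usual meanings of the name. The sample size is unaffected, and a valid between-group test is already named for each type of variable. What remains is the chance that a within-arm result is taken as evidence on ALA-SFC. The rejection rates that illustrate this depend on the assumed SD of change and on normal data; the conclusion that such a test makes no comparison with controls depends on neither.

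**What to change.** Rewrite the test sentence in section 2.6 along these lines: *Treated patients and historical controls will be compared by the Mann–Whitney U (rank sum) test for continuous variables, including urinary frequency at 3 months, and by Fisher's exact test for categorical variables. Change from baseline within patients will be described with the Wilcoxon signed rank test and will not be used as evidence of a treatment effect.* Delete the Tarone test, or state which procedure is meant, its purpose and the strata it uses.

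This costs one or two sentences, with no new data and no change in numbers.

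Optionally, because the controls are not randomised, add a between-group analysis of 3-month frequency adjusted for pretreatment urinary frequency, which the plan already collects, alongside Mann–Whitney U. That is one further sentence naming the model and the covariate; correcting the test names does not depend on it.
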